#### Other measures

At baseline, participants complete: (i) a validated VDA [44, 45]; (ii) executive function tasks of attention and working memory via the validated University of Pennsylvania Computerized Neurocognitive battery (Penn CNB [21, 46]: specifically the Penn Continuous Performance Test, the Letter N-Back test, Penn Go/No-Go task, and the Penn Abstraction and Working Memory task); (iii) a day-of performance factors survey (sleep/restfulness, caffeine and medication intake, and mood via the Positive and Negative Affect Schedule scale [47]); (iv) two impulsive personality scales: *acting-without-thinking* from the Eysenck Personality Inventory, Impulsivity Subscale [48]; and Temporal Discounting or Delay Discounting via a standard monetary reward task for children [49] (v) a Sensation Seeking scale (4-items form of the Zuckerman’s Sensation Seeking Scale [50]); (vi) a survey of demographic and household factors (vehicle access and features, living situation and household financial status indicators); (vii) items from the adolescent health risk questionnaire (risk behaviors, relationship with parents); (vii) a driving history survey (crashes and citations). In addition, demographic data from the electronic health record will be collected: age, sex, child opportunity index (COI) scores as neighborhood measures of financial status and opportunity [51]. 

During the intervention phase (i.e., learner permit to licensure), participants will receive monthly surveys to ask about their learning to drive (via the driving practice quality questionnaire [52]) and crashes and citations. Participants’ driving exposure (a confounder) will also be passively monitored via the Way to Drive app. This also has an algorithm that predicts likely crash events, which will be analyzed retrospectively as an exploratory outcome. Intervention adherence will also be tracked (via driving instructor progress reports and online e-learning platform data for online intervention progress and completion).

At the end of the learning/intervention phase, at the point of licensing examination, all participants will complete the following: (i) a second VDA; (ii) PA state licensing examination; (iii) online hazard skills test; (iv) self-report surveys of driving experience (crashes and citations), driving habits and behavior (modified driver behavior questionnaire (mDBQ) [22, 27, 53]; (vi) aggressive driving scale [54, 55]; Youth Risk Behavior Survey [55] Driving items, driving confidence scale [56]); (vii) driving practice quality questionnaire and any other ways they learned to drive beyond the interventions prescribed; and (viii) updated demographic and household factor information (update since T1). Participants who do not pass the state licensing exam initially will be given the opportunity to retake the exam for free and to continue in the trial. All participants who receive a license and remain for post-licensure phase will continue to have their driving trips monitored by the *Way to Drive* and complete surveys at 2, 4, and 6 months, capturing driving behaviors, confidence, crash history, and vehicle access (as at T2 and noted above). We will use multiple imputation and sensitivity analyses to address missing data, and we will report adherence rates for each intervention and for survey completion.

### Sample size

The target sample size for this randomized controlled trial is 1000 evaluable participants, with approximately 333 in each study arm (one group may include 334). This is based on the primary hypothesis of a reduction in hard braking events with driver training. The trial is powered to detect a 20% reduction in hard-braking events, a threshold identified by the U.S. Department of Transportation as predictive of reduced crash risk [57]. Additionally, it is designed to detect differences in state licensure exam pass rates between groups ranging from 15 to 19%, as well as an absolute increase of 10% to 13% in the proportion of drivers assigned to safer skill categories based on VDA classification. These thresholds reflect meaningful improvements in driving safety. A priori power analysis accounted for up to 20% attrition while maintaining 80% power to detect clinically meaningful effects, resulting in a worst-case scenario of 266 participants per arm. Retention strategies and participant replacement procedures are expected to mitigate attrition, leading to a final sample size of n = 800–1,000.

#### Recruitment

Adolescent learner drivers will be recruited through multiple channels. Patients identified by the Electronic Health Record (EHR) that meet the age criteria and who have an upcoming clinical visit will be contacted by the study team in advance or approached on site at the Primary care clinic visit, to share information about the study and eligibility criteria. Additional candidates may be identified through retrospective review of Adolescent Health Questionnaires indicating intent to drive within 12 months (conducted during annual adolescent wellness visits). The study team will also utilize CHOP recruitment services, the *Recruitment Enhancement Core (REC)*, to expand outreach through the EHR (EPIC). Adolescents from other CHOP primary care clinics or who respond to study fliers will also be contacted about the study. Following an initial recruitment call, written parent informed consent and child assent will be obtained, along with HIPAA authorization, via the secure REDCap electronic consent platform. Once enrolled, participants will be scheduled for baseline study visit procedures, before allocation.

### Allocation

After enrollment and baseline assessments, trial participants will be randomized into one of three cohorts in a 1:1:1 ratio so that there will be approximately 333 subjects in each arm, stratified by equal-size age categories (16 and 17) per arm. Randomization will be automatically conducted via the OnCore Clinical Trial Management System (CTMS). Allocation will be made by randomly generating block sizes of 6 and assigning individuals within an age category using the block assignments as they become available for randomization; this will be repeated until all individuals within an age group have been assigned to one of the three intervention arms.

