### Blinding

Subjects cannot be blinded to the intervention arm assignment due to the nature of the interventions (e.g., online versus behind the wheel training). For analysis, all primary outcomes are assessed in a way that is blind to intervention assignment. The Way to Drive app provides hard-braking events via automated data coding algorithms. Similarly, VDA performance is determined based on previously validated algorithms to identify driver categories [44, 45]. State license exams are conducted by independent examiners who are blinded to intervention group assignment. This is standard procedure, per state third-party testing regulations. Research staff administer the baseline surveys and other procedures before participants are allocated to an intervention arm. The cognitive battery at baseline will be electronically delivered, with accuracy and reaction time automatically recorded and scored by Penn CNB (external to the study team).

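### The only block size named is 6, within two age strata and with open arms, so about a fifth of assignments would be foreseeable to anyone who can see earlier ones

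*Protocol article*

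**What the plan says.** Under Allocation, the protocol article says that "trial participants will be randomized into one of three cohorts in a 1:1:1 ratio", "stratified by equal-size age categories (16 and 17) per arm". Randomisation runs automatically through a clinical trial management system (CTMS). The sequence is described as "Allocation will be made by randomly generating block sizes of 6 and assigning individuals within an age category using the block assignments", used as participants become available. No second block size appears.

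Under Blinding it says that "Subjects cannot be blinded to the intervention arm assignment due to the nature of the interventions", but also that "For analysis, all primary outcomes are assessed in a way that is blind to intervention assignment". On order of events, Recruitment says "Once enrolled, participants will be scheduled for baseline study visit procedures, before allocation", and Blinding adds "Research staff administer the baseline surveys and other procedures before participants are allocated to an intervention arm".

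The article does not say whether staff who book or randomise can see earlier assignments, or whether they know the block size. Methods & analysis gives August 2024 as the start of enrolment and describes data collection as ongoing.

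**The concern.** In a permuted block of fixed, known size, earlier assignments reveal later ones. The arms here are easy to tell apart: driving-school lessons against online modules. Age is the only stratification factor, so there are just two running lists to follow, and the block size is now in print. A central system hides the list, but it cannot hide what follows from past open assignments.

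Someone who knows that the next place in a stratum is, or is not, BTW could bring forward or hold back a particular teen, such as one who is keen, well resourced or easy to retain. Participant characteristics would then be linked to arm before training starts. Blind outcome assessment does not remove that, and later covariate adjustment does not do so reliably. Both primary comparisons, hard braking and first-attempt pass rate, rest on the same allocation.

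**Working it through.** **Inputs.** Block size 6, three arms, 1:1:1 and two age strata, all from Allocation. Assumption, not in the article: the observer knows the block size and every earlier assignment in the stratum. The plan gives no predictability figure to reproduce.

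**Fixed blocks of 6.** Each block is one of 6!/(2!·2!·2!) = 90 equally likely orderings. The two places of any given arm fall on any of C(6,2) = 15 pairs of positions with equal chance. At place k, k−1 places have been seen.

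- BTW ruled out: both its places are already used, C(k−1,2)/15.
- BTW ruled in: only BTW places remain. This is 1/15 at place 5 and 5/15 at place 6.
- Next arm certain: all remaining places belong to one arm. This is 3 × 1/15 at place 5, and always at place 6.
- Best guess: name the arm with most places left.

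| Place | Next arm certain | At least one arm ruled out | BTW ruled out | BTW ruled in | Best guess right |
|---|---|---|---|---|---|
| 1 | 0 | 0 | 0 | 0 | 1/3 |
| 2 | 0 | 0 | 0 | 0 | 2/5 |
| 3 | 0 | 1/5 | 1/15 | 0 | 1/2 |
| 4 | 0 | 3/5 | 3/15 | 0 | 8/15 |
| 5 | 1/5 | 1 | 6/15 | 1/15 | 3/5 |
| 6 | 1 | 1 | 10/15 | 5/15 | 1 |
| Sum | 1.2 | 2.8 | 1.333 | 0.4 | 3.367 |
| Sum/6 | 20.0% | 46.7% | 22.2% | 6.7% | 56.1% |

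BTW status is therefore certain for 22.2% + 6.7% = 28.9% of assignments. Chance guessing among three arms gives 33.3%.

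**In participants.** 20% of 1,000 is 200, and 20% of the enrolment ceiling of 1,200 is 240. These are upper figures: they include everyone randomised since August 2024, whom no change can now reach. The number still to be randomised is not given.

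**Varied block sizes.** The sizes below are illustrative and were simulated (100 runs of 999 assignments). The observer updates on every assignment and knows the possible sizes but not which one is in use. This is pessimistic if the set of sizes is withheld too.

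| Block sizes | Next arm certain | Best guess right |
|---|---|---|
| 6 only (check on the exact result) | 19.9% | 55.9% |
| 3, 6 | 8.9% | 57.6% |
| 3, 6, 9 | 3.9% | 55.4% |
| 6, 9, 12 | 2.6% | 53.0% |

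Varying the size removes most of the certainty but only a little of the guessing advantage. Mixes that include blocks of 3 keep guessing about as easy as it is now.

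**The case against.** The best case on the other side has five parts.

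- **Sight of the tally is assumed.** Nothing in the article says that staff who book visits see past assignments, or that they choose the order of entry. It says only that participants are scheduled and are assigned as they become available. Recruitment runs through several channels, and a condensed article would commonly leave access rules to the full protocol. This stands, so the size of the problem has to be stated conditionally.
- **The sentence is unclear.** It could mean randomly permuted blocks of 6, or be a compressed account of random sizes. A fixed size is the likelier reading because no other size is named, but clarification is needed either way.
- **The route is narrow.** Allocation follows consent, enrolment and baseline, so baseline measures are protected and nobody can quietly pass over a candidate who has not yet consented. What remains is delaying or reordering teens already enrolled. This also stands.
- **Allocation is central and outcomes are assessed blind.** Both are true. Blind assessment guards against detection bias, and the CTMS hides future entries. Neither prevents deduction from past open assignments.
- **Varied blocks barely change guessing.** For 3/6/9 this is right: about 55% against 56%. It argues for larger sizes and for restricting sight of the totals, not for leaving the design as it is.

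A reader might infer that upcoming assignments can in general be worked out, or that staff control who is randomised next. The documents support neither. Even a perfect tally leaves 80% of assignments uncertain, and control over order is nowhere described.

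**Conclusion.** The point holds as a modest weakness in allocation concealment. If blocks are fixed at 6 and someone involved in scheduling or randomising can follow the tally in each age stratum, the next arm is certain for 20% of assignments, BTW is ruled in or out for 28.9%, and a best guess succeeds 56.1% of the time against 33.3%. If nobody in that position sees earlier assignments, these figures do not apply.

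The percentages measure predictability, not bias. It would be wrong to read them as showing that selection has occurred or that either primary outcome is distorted; nothing in the article shows this, and no effect on an outcome can be estimated from it. The change is still worth making because it is cheap and protects those not yet randomised.

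**What to change.** For the rest of enrolment:

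1. Have the CTMS draw block sizes at random, within each age stratum, from several larger multiples of 3. With 6, 9 and 12 as an example, certainty falls to about 2.6% and best-guess success to about 53%. Sizes of 3, 6 and 9 give about 4% and 55%, so the larger set is preferable.
2. Withhold the sizes from recruiting staff, and do not publish them while enrolment is open.
3. Keep running arm totals by stratum from anyone who books baseline visits or triggers randomisation. Varied sizes leave most of the guessing advantage in place, so this step matters as much as the first.
4. Correct the sentence under Allocation to say whether blocks were fixed at 6 up to the change, and state who could see earlier assignments. If enrolment has already closed, this step alone is still useful.

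The cost is one regenerated list and a few protocol sentences, with no added participants. The possible end-of-list imbalance grows slightly. An unfinished block of 6 can leave two arms at most 2 apart, and one of 12 at most 4, so across both strata the maximum rises from 4 to 8 in a trial with about 333 per arm.

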### Blinding

Subjects cannot be blinded to the intervention arm assignment due to the nature of the interventions (e.g., online versus behind the wheel training). For analysis, all primary outcomes are assessed in a way that is blind to intervention assignment. The Way to Drive app provides hard-braking events via automated data coding algorithms. Similarly, VDA performance is determined based on previously validated algorithms to identify driver categories [44, 45]. State license exams are conducted by independent examiners who are blinded to intervention group assignment. This is standard procedure, per state third-party testing regulations. Research staff administer the baseline surveys and other procedures before participants are allocated to an intervention arm. The cognitive battery at baseline will be electronically delivered, with accuracy and reaction time automatically recorded and scored by Penn CNB (external to the study team).

### Data collection and management

The secure REDCap platform will be used for survey delivery, data storage, and collecting participant progress reports from driving school staff, as well as communication logs and study visit notes. CHOP’s CTMS will support enrollment, randomization, and participant tracking. The Department of Bioinformatics and Health Information (DBHI) and Arcus (data management and archiving service) at CHOP will provide expert data management for this trial. They will receive, manage, and link the data sets that will be honest brokered before analysis. This ensures that the research team conducting the main study analyses does not have access to any personally identifying information in the analysis dataset, while still being able to conduct the necessary analyses for the study.

### Statistical methods

Primary and secondary outcomes will be analyzed by intention-to-treat, with each outcome assessed with a separate model. Results will be interpreted based on both statistical significance (α = 0.05) and effect size, emphasizing clinically meaningful differences. As a secondary analysis, baseline covariates will be included in the model, including age at enrollment, sex, and initial VDA class. Additional factors will be examined as potential confounders (e.g., time between first VDA and licensure) and mediators (e.g., number of practice trips, miles driven, and self-reported practice quality).

To address any non-compliance in the intervention, we will use instrumental variable (IV) analysis [58], which treats the randomization assignment as the instrument. We will also consider principal stratification [59], which can relax some of the assumptions about instrumental variable analysis such as no effect of intervention assignment independent of intervention. Both of these methods attempt to estimate intervention effects among young drivers who would comply with intervention assignment regardless of assigned intervention arm. Compliance will be defined as completing more than 2/3 of the training; in the BTW arm, this would entail completing two of the three lessons. In the ACCEL and active control arms, this would entail completion of at least 2/3 of the content. In follow-up analyses, we will include the proportion of training received as a continuous measure, operationalized as the percentage of lessons completed in the assigned intervention, and utilize the mediation analyses, treating training received as a form of mediation. In all analyses we will consider log or power transformations to reduce skewness in the outcome.

Attrition is expected to be modest given the trial's retention strategies, for an estimated final sample size between 800 and 1000 participants. Participants lost before or during the intervention phase may be replaced. Participants who drop out after intervention but before the licensure exam will be encouraged to complete a second VDA. Data for available outcomes to this point will be considered for these participants, and outcomes that can be feasibly imputed will be included in analysis. For participants who fail their initial licensure exam, the study will fund a second attempt and if they pass, they will continue in the trial and follow-up data will be collected. For the rare individuals who fail the second attempt, if they go on to pass on a subsequent attempt (not provided by the study) within the study window, their follow-up data will be collected post-licensure. If the participant does not pass their licensure exam within the study window, they will not be replaced; instead, data for available outcomes will be considered for analyses, with other outcomes imputed as feasible using the data sources noted above.

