### Objectives

The primary objective of the DRIVER (DRIVer Education Research) study is to quantify the extent to which modern online driver training and BTW prior to licensure can add protection beyond GDL against crash risk early in licensure. The secondary objective is to quantify the effect of driver training on skill acquisition. The study aims and outcomes are summarized in Table 1. We hypothesize that both ACCEL and BTW training will reduce crash risk and improve driving skills compared to the control group. More specifically, we hypothesize that ACCEL will show greater improvement in crash risk and skills than BTW on the theory that ACCEL is more targeted to the critical reasons for crashes among novice adolescent drivers. However, we expect BTW to perform better on PA license examination outcomes since this test measures skills directly trained by BTW. We also hypothesize that those with weakness in cognitive and attentional control will benefit most from the training interventions in the key outcomes, and those with personality differences and risky driving practices linked to crash risk may be more resistant to the effects of driver training.

**Table 1 Tab1:** Summary of study aims and associated outcomes

Study Aim	Primary Outcome	Secondary Outcome
**Aim 1**. Determine the effect of driver training (ACCEL or BTW) compared to GDL alone on post-licensure crash risk	Hard Braking Events per 100 miles driven via Way to Drive monitoring app	• Phone Use while Driving (minutes per hour of driving) • Speeding (proportion of time > 10 miles over posted speed limit) • Self-reported crash involvement • Self-reported risky driving behavior
**Aim 2**. Determine the effect of driver training (ACCEL or BTW) compared to GDL alone on skill acquisition	Pass rate on the first attempt at the state licensing examination	• Virtual Driving Assessment (VDA) Performance at T2 • Change in T1-T2 VDA performance • Number of license exam attempts
**Aim 3**. Identify age-related risk factors for crashes that may moderate the response to training	Interactions with Aim 1 & 2 outcomes	Interactions with Aim 1 & 2 outcomes

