### Trial design

This trial uses random assignment with three parallel groups and follows an individually randomized group-treatment (IRGT) design. Participants are enrolled early in their learner permit and followed through licensure, and up to 6 months post-licensure, with the primary end point of crash risk at 2 months post-licensure. Participation length will vary with permit duration (range 8 to 18 months). After baseline, participants are randomized 1:1:1 to one of three groups (n = 333 per group): (i) professional BTW; (ii) ACCEL, a modern online driving skills training program; (iii) an active control online program covering vehicle safety topics without skills training. Participants in the BTW group will be clustered by instructor to account for variation in driver teaching style. Participants will be monitored remotely through the learner and post-licensure phases using surveys and a smartphone application capturing driving kinematics to quantify exposure and crash risk. At licensure, driving skill will be measured using three methods: the virtual driving assessment (VDA), an online hazard skills test, and results from the license examination. The primary endpoint is on-road kinematic crash risk (the rate of hard braking events) at 2 months post-licensure, with continued follow-up through 6 months post-licensure. Kinematic risky driving (KRD) events such as hard-braking events, have previously been validated as behavioral proxies for elevated crash risk [37–42]. See Fig. 1 and Table 2 for participant flow through the study and all procedures and measures through the trial.

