#### Primary outcomes

There are two primary outcomes. First, crash risk in the first 2 months of licensure (Aim 1 and 3) will be measured as the rate of hard braking events per 100 miles driving, captured via the Way to Drive smartphone app. Monitoring of hard braking events will continue through 6 months to assess crash risk at 6 months also. The app, provided by Cambridge Mobile Telematics, deploys the same algorithms as leading usage-based automobile insurance programs to measure risky driving behaviors (phone use during trips, speeding, and other kinematic risky driving measures) [38]. Second, driver skills at licensure (Aim 2 and 3) will be measured as the pass rate on the first attempt of the state licensure examination. While the state licensing exam assesses a limited set of procedural driving skills, it provides a standardized, real-world benchmark of basic driving competence and is a relevant proximal outcome for novice drivers.

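### The article ranks its primary outcomes inconsistently, and as written either of two outcomes can carry a primary claim at a flat α = 0.05

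*Protocol article*

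**What the plan says.** The protocol article describes the rank of its outcomes in two ways.

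- **Two equal primaries.** Primary outcomes states "There are two primary outcomes": the hard-braking rate per 100 miles in the first 2 months of licensure, and the pass rate at the first licence exam. The Abstract and Table 1 agree.
- **One primary.** Trial design states "The primary endpoint is on-road kinematic crash risk (the rate of hard braking events) at 2 months post-licensure". Sample size says of the target number: "This is based on the primary hypothesis of a reduction in hard braking events with driver training". Objectives makes protection against crash risk the primary objective and skill acquisition, which the exam measures, the secondary one.

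On testing, Statistical methods says "Primary and secondary outcomes will be analyzed by intention-to-treat, with each outcome assessed with a separate model", and then "Results will be interpreted based on both statistical significance (α = 0.05) and effect size, emphasizing clinically meaningful differences". The article gives no order of testing, division of α or rule linking the two outcomes. It does not list the contrasts among the three arms.

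The hypotheses in Objectives concern all three pairs of arms. Each training is expected to beat control ("We hypothesize that both ACCEL and BTW training will reduce crash risk and improve driving skills compared to the control group"), and the two trainings are compared with each other ("we hypothesize that ACCEL will show greater improvement in crash risk and skills than BTW"). On the licence exam the expected direction is reversed, in favour of BTW.

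**The concern.** A reader cannot tell from the article whether success on the exam alone would make this a positive trial. If both outcomes are primary, each is tested at the full 0.05, and either may support the claim, then the error rate for a primary claim exceeds 5%. If hard braking alone is primary, the exam result should not carry that weight. The article supports both readings.

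The ambiguity matters because the two outcomes answer different questions. The stated purpose is to inform policy on crash risk. The exam covers a narrow set of procedural skills, as the article acknowledges, and BTW is expected to do well on it because BTW trains those skills directly. Settling the rank before results are known removes any doubt about which outcome was meant to carry the conclusion.

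**Working it through.** **The plan's own figure.** Sample size gives a worst case of 266 per arm: 333 × (1 − 0.20) = 266.4, which agrees. The 80% power for a 20% reduction in hard braking cannot be reproduced, because the article gives no event rate, standard deviation or design effect. It states no family-wise error rate.

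**Inputs.** Three arms at 1:1:1 (Trial design); two primary outcomes (Primary outcomes); α = 0.05 with a model per outcome (Statistical methods). Assumed: two-sided tests, all null hypotheses true, and any one significant primary test counted as a primary claim.

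**Step 1: one three-arm test per outcome.** With independent outcomes, 1 − (1 − 0.05)² = 0.0975, or about 10%. This is the smallest reading that keeps two outcomes at full α. At a between-outcome correlation of 0.3, simulation gives 9.6%.

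**Step 2: pairwise contrasts, each at 0.05.** Contrasts that share an arm are correlated, so the rate within one outcome comes from simulation of null trials with three equal arms. Across two independent outcomes it is 1 − (1 − p)².

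| Contrasts per outcome | One outcome (p) | Two independent outcomes |
|---|---|---|
| Two against control | 9.1% | 1 − 0.909² ≈ 17% (simulated 17.3%) |
| All three pairs | 12.2% | 1 − 0.878² ≈ 23% (simulated 22.9%) |

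**Step 3: correlated outcomes.** The article gives no correlation, so a range is shown.

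| Between-outcome correlation | Two against control | All three pairs |
|---|---|---|
| 0 | 17.3% | 22.9% |
| 0.3 | 16.9% | 22.5% |
| 0.5 | 16.1% | 21.3% |
| 0.8 | 13.9% | 18.5% |

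**Step 4: power if α is split.** A contrast with 80% power at two-sided 0.05 has a standardised effect of 1.960 + 0.842 = 2.802. At 0.025 the critical value is 2.241, so power is Φ(2.802 − 2.241) = Φ(0.56) ≈ 71%.

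**Step 5: power if an omnibus test comes first.** With three arms, a 2-df test followed by pairwise tests at the same level is a closed procedure. It controls family-wise error within an outcome but costs power. Simulation of a contrast sized for 80% at an unadjusted 0.05 gives:

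| Effect in the other training arm | Power at 0.05 | Power at 0.025 |
|---|---|---|
| None, or equal | 76% | 66% |
| Half as large | 70% | 59% |

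**The case against.** The strongest reply is that this is a journal article. Contrasts, sidedness and a multiplicity procedure are commonly left to an analysis plan that is not shown here, and Statistical methods does not say that 0.05 applies to each pairwise contrast. That stands. A reader might infer that the plan fixes six primary tests and a 17–23% error rate. The documents do not support this: the six tests are read from the hypotheses, Table 1 frames Aims 1 and 2 against GDL alone, and one three-arm test per outcome fits the text equally well.

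The singular wording can also be read more mildly. The primary endpoint in Trial design may only fix the 2-month timepoint for crash risk, and the primary hypothesis in Sample size explains the sample size. But on that reading nothing orders the two outcomes, and both keep full α.

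Whether outcomes serving separate aims, or distinct trainings sharing a control, need joint error control is debated. For the arms, this is a trade-off that the sponsor may settle in the analysis plan. It does not settle which outcome is primary.

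A reader might also infer that a BTW win on the exam without a crash-risk effect would be a false positive. It would not: a real effect on the exam answers Aim 2 correctly. The problem there is the weight given to the result.

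Finally, the 80% baseline is itself uncertain. At 266 per arm, an unadjusted individual-level test at 0.05 detects at most about 12 points in pass rate (control rates 30–80%), whereas Sample size quotes 15–19%. The gap could reflect clustering or an adjustment already built in; the article does not say which.

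**Conclusion.** The concern holds in a limited form. The article contradicts itself on whether exam pass is a second primary outcome or subordinate to hard braking, and an unseen analysis plan does not remove that contradiction from this text. Taken at its word, it lets either outcome support a primary claim with a false-positive chance of about 10% under the global null, given independent outcomes and one three-arm test for each. The 17–23% range applies only if pairwise contrasts are tested unadjusted, and falls to about 14–18% at a between-outcome correlation of 0.8. It should not be cited as the trial's error rate. The point is a worthwhile, inexpensive improvement and does not undermine the design.

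**What to change.** Reconcile Objectives, Trial design, Primary outcomes, Sample size and Statistical methods, with the Abstract and Table 1 to match. Name the 2-month hard-braking rate as the sole confirmatory primary outcome at α = 0.05. Make first-attempt exam pass the key secondary, tested confirmatorily only after hard braking succeeds, and define success. This follows the ranking that Objectives, Trial design and Sample size already imply. It changes wording only and costs hard braking no α; the price is that exam pass loses co-primary rank.

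If both must stay primary, split α, for example 0.025 each, and restate power: about 71% for a contrast sized for 80% at 0.05.

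Ranking the outcomes does not deal with the three arms. Unadjusted contrasts on hard braking alone would still give 9.1% (two against control) or 12.2% (all pairs). How to handle this is the sponsor's choice, and it should be stated with its reason. An omnibus test followed by pairwise tests is valid for three arms but not free: its power, about 70–76% at 0.05 or 59–66% at 0.025 for a contrast sized for 80%, should be reported with it.
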